# Platelet-rich plasma versus corticosteroid injection for treatment of trigger finger: study protocol for a prospective randomized triple-blind placebo-controlled trial

**DOI:** 10.1186/s13063-020-04907-w

**Published:** 2020-11-27

**Keywords:** Clinical trial, Platelet-rich plasma, Trigger finger, Trigger thumb, Stenosing tenosynovitis

## Abstract

**Background:**

Trigger finger is a common hand disorder that limits finger range of motion and causes pain and snapping of the affected finger. Trigger finger is caused by an imbalance of the tendon sheath and the flexor tendon. The initial treatment is generally a local corticosteroid injection around the first annular (A1) pulley. However, it is not unusual that surgical release of the A1 pulley is required. Moreover, adverse events after local corticosteroid injection or operative treatment may occur. Platelet-rich plasma (PRP) has been shown to be safe and to reduce symptoms in different tendon pathologies, such as DeQuervain’s disease. However, the effects of PRP on trigger finger have not been studied. The aim of this single-center triple-blind randomized controlled trial is to study whether PRP is non-inferior to corticosteroid injection in treating trigger finger. The secondary outcome is to assess the safety and efficacy of PRP in comparison to placebo.

**Methods:**

The trial is designed as a randomized, controlled, patient-, investigator-, and outcome assessor-blinded, single-center, three-armed 1:1:1 non-inferiority trial. The patients with clinical symptoms of trigger finger will be randomly assigned to treatment with PRP, corticosteroid, or normal saline injection. The primary outcome is Patient-Rated Wrist Evaluation and symptom resolution. Secondary outcomes include Quick-Disabilities of the Arm, Shoulder and Hand; pain; grip strength; finger active range of motion; and complications. Appropriate statistical methods will be applied.

**Discussion:**

We present a novel RCT study design on the use of PRP for the treatment of trigger finger compared to corticosteroid and normal saline injection. The results of the trial will indicate if PRP is appropriate for the treatment of trigger finger.

**Trial registration:**

ClinicalTrials.gov NCT04167098. Registered on November 18, 2019.

## Background

Trigger finger (stenosing tenosynovitis, TF) is a condition of the tendons of the hand that causes triggering, snapping, or locking on flexion of the involved finger. TF can limit the range of motion of the affected finger and is frequently accompanied by pain in the palm of the hand [1]. TF is often considered under the category of “repetitive strain injury” [2]. The snapping of the finger is caused by the imbalance of the tendon sheath and the flexor tendon, or more precisely, thickening of the first annular pulley, the tendon, or both. Although known as tenosynovitis, no inflammatory changes have been observed in histologic studies [3]. While the condition has been recognized since 1850, the exact etiology of the condition remains unknown [4].

TF is a very common hand disorder with an incidence of approximately 3% in the general population [4]. The incidence increases to 10% among patients with diabetes [5]. Besides diabetes, gout, carpal tunnel syndrome, DeQuervain’s and Dupyutren’s disease, amyloidosis, and mucopolysaccharidosis are thought to be associated with TF [4]. TF occurs in women six times more frequently than men and is most common during the middle fifth to sixth decades of life. The ring finger is the most commonly affected finger [6].

Conservative treatment of TF is mainly based on corticosteroid injections around the tendon sheath, where it is hypothesized to decrease the tendon-sheath disproportion [7]. Nonsteroidal anti-inflammatory agents, massage, heat, ice, splinting, exercises, and stretches might also be considered as a conservative approach to relieve symptoms [8]. The short-term effect of a single corticosteroid injection has been evaluated to set between 60 and 92% [1], whereas the incidence of spontaneous recovery has been estimated to be as high as 20–29% [3]. There are three previously published randomized controlled studies comparing corticosteroid and saline injections for primary TF [9–11], advocating the use of corticosteroid injection. The short-term symptom resolution of corticosteroid versus saline injection in these studies was 54–64% versus 15–27%, respectively. While short-term results support the use of corticosteroid injection in primary TF, the efficacy seems to decrease over time and the long-term evidence is insufficient [12, 13].

If conservative treatment of TF fails or symptoms recur, and the patient is compliant, surgical release of the A1 pulley should be considered [14]. Surgical release of the pulley structure may be executed in an open, percutaneous, or endoscopic manner with uncertain comparative evidence; open release is the most used and traditional method [4].

Platelet-rich plasma (PRP) has been shown to reduce symptoms in different tendon pathologies [15, 16] and seems to be superior to cortisone [17–19]. PRP therapy is safe and feasible [20] but does not reverse the degenerative tendon changes [21]. On the other hand, cortisone treatment is not a long-term solution due to the relatively high recurrence rates after injections [22] and can cause adverse events in patients [23].

Considering the possible adverse events relating to open or percutaneous TF surgery [24], novel methods should also be considered. As PRP therapy seems to be safe and effective in many tendon pathologies, we designed a prospective placebo-controlled randomized trial to evaluate the possible benefits of PRP therapy in TF treatment. Our primary hypothesis is that PRP is non-inferior to cortisone measured with symptom resolution and Patient-Rated Wrist Evaluation (PRWE). The secondary hypothesis of this trial is that single injection of PRP is superior compared to placebo in the treatment of TF.

## Methods/design

### Trial hypothesis

Our primary hypothesis is that PRP is non-inferior to cortisone, and the secondary hypothesis of this trial is that single injection of PRP is superior compared to placebo in the treatment of TF. The primary endpoint is the Patient Rated Wrist Evaluation (PRWE) score and symptom resolution at 6 months post-injection. This will also be the timepoint for unveiling the primary allocation. Secondary objectives include Quick-Disabilities of the Arm, Shoulder and Hand (Q-DASH); pain (Visual Analogue Scale, VAS); grip strength; active range of motion (ROM); rate of adverse events; and global improvement.

### Trial design

The trial is designed as a randomized, controlled, patient-, investigator-, and outcome assessor-blinded, single-center, three-armed 1:1:1 non-inferiority trial. The CONSORT diagram of the trial cohort is presented in Fig. 1.

**Fig. 1 Fig1:**
[figure not shown]
CONSORT diagram of the trial

### Participant characteristics

We will assess the eligibility of all patients with TF that are referred to Helsinki University Hospital. These participants will be screened according to the inclusion and exclusion criteria. A recruitment investigator (RI) will confirm the clinical diagnosis of TF. The diagnosis is based on the following clinical findings: tenderness/pain over the flexor tendon sheath (A1 pulley), thickening or swelling of the tendon and/or the tendon sheath, and triggering or snapping of the affected finger. To qualify as a RI, all trial physicians must have experience of treating more than 200 cases of TF before the start of the trial.

Patients eligible for this trial will receive written information. The RI will obtain consent from the participants and collect baseline data prior to the randomization. The eligibility criteria are presented in Table 1. Participation in the trial is voluntary, and withdrawal is allowed at any time. In case of inadequate symptom relief after injection, the allocation will be unveiled. The patient will be offered either a corticosteroid injection (cross-over or second injection) or open surgery under local anesthesia, but preferably not before 6 months after the initial treatment.

**Table 1 Tab1:** Trial eligibility criteria

Inclusion criteria (all of the following)	Exclusion criteria (any of the below)
Age 18–75	Diabetes
Trigger finger in 1–2 rays of the affected hand	Trigger finger in > 2 rays of affected hand
Symptom duration > 3 months	Rheumatoid arthritis or other condition requiring continuous oral corticosteroids
	Previous history of surgery or injection in the affected ray
	Dupuytren’s disease of the affected hand
	Alcohol or drug abuse
	Mental instability

### Preparation of PRP, corticosteroid, and placebo

PRP is prepared according to the manufacturer’s instructions (Regen Lab SA, Switzerland). Each voluntary patient eligible for the trial will have 10 ml of fresh venous blood withdrawn in a sterile manner into PRP tubes by a research nurse to ensure blinding of the treatment. The nurse will then move to another room, randomize the patient, and prepare the product indicated by the randomization. After centrifugation, 0.5 ml of ready-made PRP will be used. The corticosteroid group will receive 0.5 ml of Depo-medrol, and the control group will receive 0.5 ml of 0.9% saline. The syringe used will be taped by the nurse with sterile opaque tape and provided to the investigator. To ensure concealment, the research nurse will not participate further in the treatment or follow-up of the patients.

### Outcome measures

The primary enpoints are PRWE and symptom resolution at 6 months post-injection. Secondary outcomes include Q-DASH, pain on Visual Analogue Scale (VAS, 0 = no pain, 10 = worst imaginable pain), grip strength, finger active range of motion (ROM), and global improvement. The possible recurrence of TF symptoms will be registered. After initial treatment, follow-up will take place at 1, 3, 6, 12, and 24 months post-treatment. The trial schedule of enrolment, interventions, assessments, and data collection is presented in Fig. 2.

**Fig. 2 Fig2:**
[figure not shown]
The schedule of enrolment, interventions, assessments, and data collection. PRP, platelet-rich plasma; PRWE, Patient-Rated Wrist Evaluation; Q-DASH, Quick-Disabilities of the Arm, Shoulder and Hand; ROM, finger active range of motion; VAS, Visual Analogue Scale. * = primary endpoint of the study

#### Patient-Rated Wrist Evaluation

The Patient-Rated Wrist Evaluation (PRWE) is a simple standardized outcome measure for wrist and hand pathologies that is easy to administer and score in clinical practice. The PRWE is a 15-item questionnaire designed to measure pain and disability in activities of daily living [25]. The Finnish version has been translated, culturally adapted, and validated [26].

#### Symptom resolution

Symptom resolution is a consensus between the patient and doctor on the perceived benefit of the treatment and is rated as follows: 0 = no response; 1 = partial response, but not satisfactory, warranting further treatment; 2 = partial response, satisfactory, not warranting further treatment; and 3 = complete resolution of symptoms and signs.

#### Quick-disabilities of the Arm, Shoulder and Hand

The Quick-Disabilities of the Arm, Shoulder and Hand (Q-DASH) is a 11-item questionnaire that considers the upper extremity as one functional unit [27]. It is a widely used reference for self-reported disability in various pathologies that affect the upper limb. Similar to the PRWE, the Finnish version has been translated, culturally adapted, and validated [28].

#### Pain

The Visual Analogue Scale (VAS) consists of a straight line with endpoints that define extreme limits to experiencing pain, from “no pain at all” and “pain as bad as it could be” [29]. The subject is asked to mark their pain level on the line between the two endpoints. The distance between “no pain at all” and the mark defines the subject’s pain. The VAS is a validated and reliable tool in pain assessment and is easy to use [30].

#### Grip strength and finger range of motion

Grip strength will be determined with a dynamometer (JAMAR hand dynamometer Model J00105, Lafayette, IN, 47903, USA). Finger active range of motion (ROM) will be measured using a manual goniometry. In addition to thumb interphalangeal joint goniometry, thumb active ROM is measured by using the Kapandji thumb opposition score (Fig. 3) [31].

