**Fig. 3 Fig3:**
[figure not shown]
Kapandji thumb opposition score (0 = no opposition, 10 = maximal opposition)

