#### Statistical plan

Statistical analysis will be performed with an intention-to-treat method. A statistical software program will be used for analyzing entered data (IBM SPSS Statistics for Windows, Version 25.0. Armonk, NY: IBM Corp. 2017). Blinded data interpretation will be used to diminish interpretation bias; therefore, the biostatistician will be unaware of the group assignments when performing the analyses [34].

Descriptive statistics will be presented as mean (standard deviation) or median (interquartile range) for continuous variables and count (percent) for categorical variables. Levene’s test will be used to examine the homogeneity of variance between groups, and Welch’s or Student’s *t* test will be used to compare the point estimates for the means of the intervention groups. Ninety-five percent confidence intervals will be calculated for the mean difference. Chi-square test or Fisher’s exact test will be used to assess categorical data. Repeated measures will be analyzed using generalized linear mixed models.

The criterion for statistical significance will be set at *p* = 0.025 (one-sided) or *p* = 0.05 (two-sided). All *p* values will be reported to three decimal places with those less than 0.001 reported as *p* < 0.001.

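### Range of motion is one secondary outcome for fingers and thumbs measured differently, and the only stated comparison of means is an unadjusted t test, which can lose modest to severe power

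*Protocol article*

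**What the plan says.** Under Outcome measures, the protocol article lists among the secondary outcomes "grip strength, finger active range of motion (ROM), and global improvement". ROM has a single entry there and again among the key secondary outcomes in Table 2.

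Under Grip strength and finger range of motion, "Finger active range of motion (ROM) will be measured using a manual goniometry". The finger joints and the summary over joints are not named. For the thumb, "In addition to thumb interphalangeal joint goniometry, thumb active ROM is measured by using the Kapandji thumb opposition score". The caption of Fig. 3 gives that scale as "Kapandji thumb opposition score (0 = no opposition, 10 = maximal opposition").

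Table 1 admits "Trigger finger in 1–2 rays of the affected hand" and does not exclude the thumb. Trigger thumb is also one of the article's keywords.

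Under Statistical plan, after Levene's test, "Welch’s or Student’s *t* test will be used to compare the point estimates for the means of the intervention groups". That section also says "Repeated measures will be analyzed using generalized linear mixed models", without naming covariates. Randomization and concealment describes permuted blocks of variable size and mentions no stratification by digit.

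**The concern.** One outcome label covers two kinds of digit that are measured at different joints, and the thumb has an extra score on another scale. A finger's active motion, if summed over its joints, and a thumb's interphalangeal motion can differ by many degrees in patients who respond equally well. In a t test on raw degrees that difference counts as noise.

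What is at stake is precision in one of the two objective function measures, the other being grip strength. The secondary hypothesis is that PRP is superior to placebo. An imprecise ROM comparison could be read as showing no difference when it could not have detected one.

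**Working it through.** **Plan's own figure.** None is given for ROM. The Sample size section plans 32 per group for the Patient-Rated Wrist Evaluation (margin 11.5, SD 14, power 90%, one-sided 2.5%). This reproduces: 2 × 14² × (1.960 + 1.282)² / 11.5² = 31.1, rounded up to 32. I use 32 per arm and the plan's two-sided 5% level.

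**Assumed inputs (none is in the article).**
- Within-digit SD, s: 20 to 30 degrees.
- Finger mean minus thumb mean, D: 60 to 180 degrees. The range is wide because the finger joints and summary are not named.
- Thumb share, p: 10 to 40%.
- True difference between arms: 20 degrees.

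**Step 1: pooled SD** = √(s² + p(1−p)D²).
- Mildest corner (s = 20, D = 60, p = 0.1): √(400 + 0.09 × 3,600) = √724 = 26.9 degrees.
- Most severe corner (s = 30, D = 180, p = 0.4): √(900 + 0.24 × 32,400) = √8,676 = 93.1 degrees.

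**Step 2: power.** The standard error is SD × √(2/32) = SD × 0.25, and power ≈ Φ(20/SE − 1.96).

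| Case | SD | SE | Power for 20 degrees |
|---|---|---|---|
| Pooled, mildest | 26.9 | 6.7 | 84% |
| Pooled, most severe | 93.1 | 23.3 | 14% |
| Digit type separated, s = 20 | 20 | 5.0 | 98% |
| Digit type separated, s = 30 | 30 | 7.5 | 76% |

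Like for like, the mildest corner falls from 98% to 84% and the most severe from 76% to 14%.

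**Step 3: difference detectable with 80% power** = (1.96 + 0.84) × 0.25 × SD. This is 19 to 65 degrees pooled, against 14 to 21 degrees with digit type separated.

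**Step 4: chance imbalance in thumbs.** One SD of its effect on the arm difference is D√(2p(1−p)/32), which runs from 4.5 degrees (D = 60, p = 0.1) to 22 degrees (D = 180, p = 0.4). This is the between-digit part of the standard error in step 2, so it is not a second harm.

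**Step 5: simulation** (8,000 runs per row; s = 25, correlation 0.5 between baseline and follow-up, true difference 20 degrees).

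| Thumbs | D | Raw t test | Change from baseline | ANCOVA on baseline | Digit type only | Baseline and digit type |
|---|---|---|---|---|---|---|
| 25% | 180 | 16% | 88% | 88% | 88% | 95% |
| 25% | 60 | 58% | 88% | 91% | 88% | 95% |
| 10% | 60 | 72% | 88% | 93% | 87% | 95% |

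With no true difference (25% thumbs, D = 180), the raw t test rejects in 5.2% of runs and the model with both terms in 4.9%. With a true difference of 20 degrees, the mean raw estimate is 19.97. Pooling therefore costs precision and brings no bias or type I inflation.

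**The case against.** The strongest reply is that the article never says the measures are put into one mean. It describes the Kapandji score as an additional thumb measure, and a separate analysis of it is the natural reading. A reader might infer that Kapandji points are averaged with degrees. The text does not support that, and the point does not need it: finger degrees and thumb interphalangeal degrees under one label are enough.

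Second, the t-test sentence is general. It does not mention ROM or raw follow-up values, and mixed models are planned for repeated measures. This stands, and it is why the conclusion is conditional on pooling raw values. It does not remove the point, because no digit term, baseline term or change score is named for either method.

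Third, joints, summaries and covariates for a secondary outcome are often left to an analysis plan. That is fair, and their absence alone would be no finding. Here, though, the article itself sets the measurement by digit, the single label and the test, and a better analysis is available at almost no cost.

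Fourth, every ROM input is assumed, and the gap D drives the result. If finger ROM were read at a single joint, the gap could be much smaller than for a sum over joints. The range of 60 to 180 degrees shows how far this matters.

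A reader might also infer that the unstratified allocation biases the comparison. It does not: randomization balances thumbs in expectation.

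**Conclusion.** The point holds as a conditional loss of precision in a secondary outcome. If finger and thumb degrees are compared as raw values in one mean, power for a 20-degree difference is about 14 to 84%, against 76 to 98% with digit type separated, over the assumed ranges. The loss is modest with few thumbs and a small gap, and severe with many thumbs and a large gap.

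A reader might go further and infer that the thumb share would bury any treatment effect, or that the trial could not tell PRP from saline or corticosteroid on ROM. Neither follows. A 30-degree difference keeps 25 to 99% power even when pooled, over the same ranges, and the estimate stays unbiased with type I error at 5%. ROM is also not part of the primary hypothesis or the sample size calculation. This is an inexpensive improvement and no threat to the trial's main conclusion.

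**What to change.** Add one sentence to the statistical plan before unblinding: ROM in degrees of the treated digit will be compared between arms in a model (ANCOVA, or the mixed model already planned) that includes baseline ROM and digit type (thumb or finger), and the Kapandji score will be reported separately, in thumbs only. The sentence should also name the finger joints and summary used and, since Table 1 allows two affected rays, which digit supplies the value.

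The fix assumes that ROM is among the baseline data collected before randomization. The schedule in Fig. 2 is not shown, so I could not confirm this. Digit type is known in any case, and adjusting for it alone recovers most of the loss (87 to 88% in the simulation). The cost is slightly more analysis work, with no new measurement, visit or change to treatment.

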**Fig. 3 Fig3:**
[figure not shown]
Kapandji thumb opposition score (0 = no opposition, 10 = maximal opposition)

#### Global improvement

Global improvement is a patient-centered standpoint of perceived benefit of the intervention. Global improvement is evaluated using five-step Likert scale from (− 2) “Much worse” to (+ 2) “Much better.”

#### Adverse events

Complications will be reported. Tendon, nerve, arterial injury, chronic regional pain syndrome, infection, hematoma, or any other condition that can be attributed to the intervention will be regarded as adverse events (event needing intervention or not disappearing).

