Date of first enrolment	April 9, 2020
Target sample size	117
Recruitment status	Recruiting
Primary outcome(s)	Symptom resolution (rate of success), Patient-Rated Wrist Evaluation
Key secondary outcomes	Quick-Disabilities of the Arm, Shoulder and Hand; pain (Visual Analogue Scale); global improvement; grip strength; finger range of motion (ROM); complications

*PRP* platelet-rich plasma

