## Discussion

An increasing interest in biologic agents as nonoperative treatment modalities or to augment surgical procedures has been observed in recent years. One of these, PRP, has been shown to reduce symptoms in different tendon pathologies with the rationale to potentially accelerate the healing process [38].

PRP has positive effects on both short-term and long-term pain on tendon and ligament healing [39]. PRP contains various growth factors that have potential tendon-healing properties [38]. PRP has been previously used in hand pathologies such as osteoarthrosis [40]. Furthermore, Ramesh et al. [41] reported a 77% success rate after one and a 93% success rate after two doses of autologous PRP for the treatment of DeQuervain’s disease. The effects of PRP on TF have not yet been studied.

Digital stenosing tenosynovitis (i.e., TF) is a common example of a tendon pathology caused by the imbalance of the flexor and its sheath. Injection of corticosteroids in the vicinity of the A1 pulley is generally accepted as a first-line therapy, although recurrence rates up to 33% have been reported [1]. Moreover, up to 5.8% of major adverse events have been reported in soft-tissue injections of cortisone (defined as those needing intervention or not disappearing) [23]. As some authors have stated superiority of PRP compared to cortisone in select musculoskeletal disorders [17–19], investigating the clinical efficacy of PRP in treating TF is warranted.

Despite the increasing interest and use of PRP in clinical orthopedics, there are still concerns regarding its clinical efficacy due the lack of high-quality randomized controlled trials. Contradictory results have also been observed. A participant-, investigator-, and assessor-blinded, placebo-controlled, randomized trial setting is the reference standard in trial designs. Thus, we conceived this trial to assess the effectiveness of PRP intervention in treating TF of the digits in a high-quality trial setting by measuring patient-rated outcomes, symptom reduction, and improvement of function. Moreover, to the best of our knowledge, this study is the first clinical trial to assess the use of PRP in TF.

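### The definition of an adverse event is the threshold the protocol elsewhere calls major, so untreated self-limiting events drop out of the adverse-event rate

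*Protocol article*

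**What the plan says.** The Adverse events section opens with an unqualified statement, "Complications will be reported". It then names tendon, nerve and arterial injury, chronic regional pain syndrome, infection and hematoma, adds a catch-all for other attributable conditions, and says that these "will be regarded as adverse events (event needing intervention or not disappearing").

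The Discussion describes earlier experience with corticosteroid, where "major adverse events have been reported in soft-tissue injections of cortisone (defined as those needing intervention or not disappearing"). The qualifier is the same, but there it marks out major events.

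Safety is a declared aim. The Abstract's Background states: "The secondary outcome is to assess the safety and efficacy of PRP in comparison to placebo". The Trial hypothesis section ends its list of secondary objectives with "rate of adverse events; and global improvement". The registry table under Ethics and dissemination uses a different term and ends its key secondary outcomes with "grip strength; finger range of motion (ROM); complications". The Abstract's Methods paragraph also lists complications.

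**The concern.** A severity threshold has become the entry condition for being an adverse event at all. The protocol defines no lesser category, so an event below the threshold has no stated place in the adverse-event rate.

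This matters because the argument for PRP rests partly on the harms of corticosteroid and surgery, and because Ethics and dissemination already describes PRP as inherently safe. If only major events count, a low rate in every arm follows partly from the definition. A difference between PRP, corticosteroid and saline in short-lived local reactions would not show in the rate that is meant to describe safety.

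**Working it through.** The point concerns a definition, and the protocol gives no figure for the safety comparison, so there is none to reproduce. The check applies the rule to cases.

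**Step 1. The rule.** An occurrence counts if it is on the named list, or can be attributed to the intervention, and if it either requires treatment or persists.

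**Step 2. Two readings.** The parenthesis follows the words adverse events and begins with the word event, so the natural (broad) reading is that it governs everything in the sentence. A narrow reading lets it qualify only the catch-all.

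| Case | Needs intervention | Persists | Broad reading | Narrow reading |
|---|---|---|---|---|
| Infection, treated, clears | yes | no | counted | counted |
| Nerve injury, untreated, lasting | no | yes | counted | counted |
| Hematoma, untreated, resolves | no | no | **not counted** | counted |
| Local reaction not on the list, untreated, resolves | no | no | **not counted** | **not counted** |

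The last row is lost on either reading. The third is lost only on the broad one.

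**Step 3. Comparison with the Discussion.** The same test, treatment or persistence, defines major events there. The Adverse events section omits the word major and supplies no second tier.

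**Step 4. Consequence for the endpoint.** The secondary objective is the rate of adverse events, and the Adverse events section is the only place that defines the term. What that definition excludes is therefore absent from the rate.

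**Step 5. Whether another outcome fills the gap.** Pain on the VAS is collected separately, but the first follow-up under Outcome measures is at 1 month. A reaction confined to the days after injection would not appear there.

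**Step 6. Scale, by assumption only.** With 117 patients allocated 1:1:1, each arm has 117/3 = 39. The documents give no rate for untreated self-limiting reactions. If a share r of an arm has one, the number affected is 39 × r:

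- r = 5%: 39 × 0.05 = 2.0
- r = 20%: 39 × 0.20 = 7.8
- r = 40%: 39 × 0.40 = 15.6

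These figures show a possible range. They are not estimates for PRP, corticosteroid or saline.

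**The case against.** Several points on the other side have force.

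- **Complications are to be reported without a filter.** This stands in part: some minor events may be written down under that term. But complications is never defined, and the listed objective in Trial hypothesis is the adverse-event rate. Two safety terms of apparently different scope are left unreconciled.
- **The sentence is ambiguous.** This also stands in part. The attribution clause may modify only the catch-all, so the named injuries may need no attribution judgement, and the parenthesis may be equally local. Unlisted self-limiting reactions are still excluded.
- **Recording fields belong in the full protocol.** Agreed, and their absence from a journal article is not the complaint. The complaint is about a definition that the article does state.

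A reader might also infer three stronger things that the documents do not support.

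- **That all transient harm is missed.** It is not. A transient event that needed treatment meets the test and counts.
- **That the interim safety review is deprived of data.** Data management and monitoring bases oversight on the collected outcome data and acts on any safety concern. It does not restrict the review to events meeting this definition.
- **That the cited corticosteroid rate sizes the problem.** The Discussion says "up to 5.8% of major adverse events have been reported in soft-tissue injections of cortisone (defined as those needing intervention or not disappearing"). That is an upper figure for major events after soft-tissue corticosteroid injection. Major events are counted now and would be counted after any repair, so the figure says nothing about the events left out.

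Nor do the documents show that attribution would hide a difference between arms. The recruitment investigators are blinded, and the wording asks only whether an event can be attributed. Blinding is less secure later, since the allocation is unveiled at 6 months, or earlier on request, while follow-up runs to 24 months. That is a reason to record relatedness separately, not evidence of bias.

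**Conclusion.** The concern holds in a limited form. The Adverse events section applies to all adverse events the threshold that the Discussion gives for major ones. Read literally, self-limiting events that need no intervention are left out of the adverse-event rate, and the safety comparison of PRP with placebo is weaker for it. The conclusion assumes that the rate will be compiled from the definition as written. For a resolving hematoma it also assumes that the parenthesis covers the named list; for unlisted reactions it does not depend on that.

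The number of events lost cannot be derived from the documents. The primary endpoints, the sample size and the primary analysis are untouched. The repair should be made because safety is a declared aim and the change is cheap, but the point does not threaten the trial's main conclusion.

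**What to change.** Amend the Adverse events section as follows.

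1. Give the present threshold the name major adverse event.
2. Define an adverse event as any untoward event in any arm, regardless of attribution, need for intervention or resolution.
3. At the existing visits (1, 3, 6, 12 and 24 months), ask about events since the last contact. Judge relatedness blind to arm where possible and record it separately from the event.
4. Report both the all-event rate and the major-event rate by arm.
5. Say how complications relates to these two terms, or replace it with them in the Abstract and the registry table.

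The cost is a few sentences of protocol text and slightly more data entry, with no added visit and no change to treatment, sample size or primary analysis. One limitation remains: with the first visit at 1 month, brief post-injection reactions would rest on patient recall. Recruitment had already begun when version 1.2 was dated, so the report should state from which date the wider definition applied.
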